### Outcome measures

*Primary endpoint:*

**Infection** defined according to the PANTHERIS study
[26]: I) pneumonia was defined as presence of at least one of the A and one of the B criteria: A) abnormal respiratory examination, pulmonary infiltrates in chest X-Ray; B) productive cough with purulent sputum, microbiological cultures from lower respiratory tract or blood cultures, leukocytosis, and elevation of CRP. II) Urinary tract infection was defined as the presence of two of the following criteria: fever (>38.0°C), urine sample positive for nitrite, leucocyturia, and significant bacteriuria. III) Infection was also diagnosed if temperature was above 38.0°C on at least 2 determinations with additional leucocytosis and positive blood cultures, but no determined focus.

*Secondary endpoints:*

– **SIRS:** criterium II according to Guidelines of the German Sepsis Society

– **Severe sepsis***:* criteria I, II and III according to Guidelines of the German Sepsis Society

– **Functional outcome**: day 5 and 3 months after insult (modified Rankin Scale, Barthel Index)

The cumulative incidence of infections, SIRS or severe sepsis will be estimated up to day 5 after the onset of stroke.

Guidelines of German Sepsis Society

I. **Confirmation of infection**

• Diagnosis of an infection on the basis of microbiological evidence or clinical criteria

II. **Systemic inflammatory host response (SIRS) (at least 2 criteria)**

• Fever (**≥**38°C) or hypothermia (**≤**36°C) confirmed by rectal, intravascular or intravesical measurement

• Tachycardia: heart rate **≥**90 bpm

• Tachypnea (frequency **≥**20/min) or hyperventilation (PCO2 **≤**4.3 kPa/ **≤**33 mmHg)

• Leukocytosis (**≥**12000/mm3) or leukopenia (**≤**4000/mm3) or **≥**10% immature neutrophils in differential blood count

III. **Acute organ dysfunction (at least 1 criterion)**

• Acute encephalopathy: reduced alertness, disorientation, agitation, delirium

• Relative or absolute thrombocytopenia: decrease in platelet counts by more than 30% within 24 hours or a platelet count of less than 100.000/mm3. Thrombocytopenia due to acute hemorrhage or immunological causes must be ruled out.

• Arterial hypoxemia: PaO2 **≤**10 kPa (**≤**75 mmHg) while breathing ambient air or a PaO2/FiO2 ratio of **≤**33 kPa (**≤**250 mmHg) on oxygen administration. A clinically manifest heart or lung disease must be ruled out as a cause of hypoxemia.

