### Statistical analysis

HRV risk indices (predictors) will be calculated from selected intervals of 24 h ECG measurements according to standards and procedures previously developed and published by the applicant. The predictive effects of HRV indices on infections will be estimated by fitting logistic regression models and estimating odds ratios with 95% confidence intervals. A prespecified modelling procedure will be applied to estimate unadjusted and confounder adjusted odds ratios. Secondary endpoints will be analysed in the same way. The functional outcome scales will be dichotomized. The association between HPV indices and pro- and anti-inflammatory molecular markers will be quantified by calculating the appropriate correlation coefficients according to scale (Person or Spearman).

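### As defined, the severe sepsis endpoint lets the index stroke itself supply the organ-dysfunction component through the encephalopathy item

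*Protocol article*

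**What the plan says.** Protocol article, Outcome measures, defines severe sepsis as "criteria I, II and III according to Guidelines of the German Sepsis Society". Criterion I is infection. Criterion II is "Systemic inflammatory host response (SIRS) (at least 2 criteria") from a list of four, one of which begins "Tachycardia: heart rate" with a threshold of 90 bpm. Criterion III is "Acute organ dysfunction (at least 1 criterion") from a list of five.

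The first item under III is "Acute encephalopathy: reduced alertness, disorientation, agitation, delirium". Two later items tell the assessor to exclude other explanations. For platelets: "Thrombocytopenia due to acute hemorrhage or immunological causes must be ruled out". For oxygenation: "A clinically manifest heart or lung disease must be ruled out as a cause of hypoxemia".

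Study population admits patients with middle cerebral artery infarction and NIHSS of at least 8. Under Statistical analysis, "Secondary endpoints will be analysed in the same way" as the primary endpoint: logistic regression on the HRV indices, unadjusted and adjusted. Methods against bias names baseline NIHSS, infarct size and infarct location among the potential confounders.

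The outcome window is stated in two ways. The Abstract places SIRS and severe sepsis on days 3 to 5. Outcome measures counts them cumulatively to day 5 and gives no starting day.

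**The concern.** Component III should separate infection with SIRS from infection with SIRS and septic organ failure. Reduced alertness or disorientation can be a direct result of the infarct that qualified the patient. The word acute in the item does not help, because the stroke is acute too. Taken as printed, an infected patient with SIRS whose alertness was already reduced on arrival counts as severe sepsis although no organ has failed because of the infection.

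The odds ratio reported for severe sepsis would then partly describe infection plus SIRS in patients with more disabling strokes. Misclassification of this kind would probably rise with stroke severity, which the article itself treats as a potential confounder.

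A smaller issue concerns SIRS. One of its items is heart rate, and the predictors come from the same cardiac rhythm. If the outcome window includes the predictor recording, tachycardia during the Holter can count towards the outcome it is meant to predict.

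**Working it through.** **Plan's own figures.** The article states no rate for SIRS, encephalopathy or severe sepsis, so there is no such figure to reproduce. The sample-size chain for the primary endpoint does reproduce: the 1989 Hsieh formula for logistic regression (OR 0.4 per SD, 35% infections, two-sided 0.05, 80% power) gives 81.2, hence 82. Then 82/(1 − 0.4) = 136.7 (stated 136), and 136/0.57 = 238.6 (stated 240).

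**Which components the stroke can meet.**
- I (infection): no.
- II (SIRS): heart rate alone is not enough, since two items are needed.
- III (organ dysfunction): yes, because one item suffices and encephalopathy has no attribution condition.

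**Size for severe sepsis.** Inputs from the Sample size section: 136 analysable patients and 35% infected, so 136 × 0.35 = 47.6 infections. The remaining inputs are assumptions:
- s = share of infected patients with SIRS, 40% to 80%
- d = genuine organ dysfunction among those, 10% to 30%
- e = stroke-related reduced alertness or disorientation, 10% to 80%, independent of d

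Formulas:
- genuine cases = 47.6 × s × d
- counted cases = 47.6 × s × [1 − (1 − d)(1 − e)]
- share meeting III only through the stroke = 1 − d/[1 − (1 − d)(1 − e)]; s cancels

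| d | e | 1 − (1 − d)(1 − e) | Share through stroke only |
|---|---|---|---|
| 0.3 | 0.1 | 1 − 0.7 × 0.9 = 0.37 | 1 − 0.30/0.37 = 19% |
| 0.2 | 0.1 | 1 − 0.8 × 0.9 = 0.28 | 1 − 0.20/0.28 = 29% |
| 0.2 | 0.5 | 1 − 0.8 × 0.5 = 0.60 | 1 − 0.20/0.60 = 67% |
| 0.1 | 0.8 | 1 − 0.9 × 0.2 = 0.82 | 1 − 0.10/0.82 = 88% |

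Counted cases run from 47.6 × 0.4 × 0.19 = 3.6 (d = e = 0.1) to 47.6 × 0.8 × 0.86 = 32.7 (d = 0.3, e = 0.8). Genuine cases run from 47.6 × 0.4 × 0.1 = 1.9 to 47.6 × 0.8 × 0.3 = 11.4. Without infection, or with fewer than two SIRS items, the count is zero whatever e is.

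**Timing for SIRS.** The Holter starts at most 24 h after onset and runs 24 h, so it may last until 48 h. A window of days 3 to 5 follows it. A cumulative count to day 5 with no start can overlap it.

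**Weight of the heart-rate item.** Assume fever 25%, tachypnea 30% and the leukocyte item 20%, mutually independent and unrelated to HRV.
- P(two or more of these three) = 0.060 + 0.035 + 0.045 + 0.015 = 0.155
- P(exactly one) = 0.140 + 0.180 + 0.105 = 0.425
- Tachycardia 20%: 0.425 × 0.2 = 0.085; 0.085/(0.155 + 0.085) = 35% of SIRS cases need the heart-rate item.
- Tachycardia 40%: 0.425 × 0.4 = 0.170; 0.170/(0.155 + 0.170) = 52%.

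In a simulation of 400,000 patients per scenario, a correlation of 0.2 between an HRV index and the heart rate behind this item gave an OR per SD of 1.14 to 1.17. A correlation of 0.4 gave 1.31 to 1.36. With the opposite sign these become reciprocals. At zero correlation the OR was about 1.

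**The case against.** The strongest reply is that these are published guideline criteria, that an item headed acute leaves room for clinical judgement, and that the study manual or analysis plan, neither shown, may contain an attribution rule. The contrast with other items is also incomplete, since metabolic acidosis has no exclusion clause either. This has some force, but the article prints the whole rule, including exclusions for two items. The item most exposed to the qualifying disease has none, so the fault lies in stated text and is not an omitted detail.

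Other objections limit the point:
- A reader might infer that the stroke alone can produce severe sepsis. It cannot, because infection and SIRS are still required.
- NIHSS is a total score, so a value of 8 or more does not establish reduced alertness. A several-fold excess follows only from a high assumed rate: with d = 20%, a rate of 50% gives 0.60/0.20 = 3-fold, but 10% gives 0.28/0.20 = 1.4-fold.
- A reader might infer that the error must favour the hypothesis. The documents do not show this. The Background describes sympathetic dominance with reduced vagal HRV after stroke, whereas in the feasibility study lower LFnorm and higher HFnorm preceded infection. If severity strengthens the first pattern, bias for these two indices would oppose the hypothesis; only for VLF does the direction agree.
- Planned adjustment for NIHSS may reduce confounding by severity. It does not reclassify a wrongly counted case.
- A reader might infer that SIRS is contaminated by construction. The predictors are variability indices, not mean heart rate, and heart rate alone never meets SIRS. If the window starts after the recording, only persisting autonomic state links the two, and predicting through that is not spurious in a prognostic study.

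**Conclusion.** The point holds for severe sepsis. The printed rule allows the index stroke to satisfy component III in some patients, and for them the endpoint becomes infection plus SIRS. The size cannot be fixed from the documents. The range of 19% to 88% of counted cases rests on the assumed rates above and on independence between stroke-related encephalopathy and genuine organ dysfunction. Even the low end matters for an endpoint with so few expected events. The direction of any resulting bias in the HRV odds ratios is open.

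For SIRS the finding is narrower: two statements of the outcome window conflict, and one of them lets the outcome overlap the predictor recording.

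The primary endpoint contains neither encephalopathy nor heart rate. It, functional outcome and the sample size stand as they are. The change should be made, but it concerns secondary endpoints only.

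**What to change.** 1. In the severe sepsis definition, count encephalopathy only when it is new or worse than the baseline neurological status; otherwise require one of the other four listed organ items. Report the unmodified guideline definition as a supportive analysis.
2. Reconcile the Abstract with Outcome measures so that the SIRS and severe sepsis window starts after the predictor Holter ends.
3. Add a sensitivity analysis of SIRS without the heart-rate item.

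The cost is mainly wording plus analyses of data largely collected already: Key data acquisition records neurological status, including NIHSS, at each daily visit to day 5. The article does not say whether agitation or delirium is recorded separately, so that should be checked. The price is a small departure from the guideline wording and fewer severe sepsis events (1.9 to 11.4 genuine cases under the assumptions above), which limits how many covariates an adjusted model for this endpoint can carry.

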### Further analysis

Correlation analysis between HRV indices (LFnorm, HFnorm, VLF) and pro- and anti-inflammatory molecular markers (copeptine, PCT, CRP, IL-6, IL-10, mHLA-DR, TNF alpha) daily taken at day 1 to day 5.

The predictive value of Autonomic Information Flow (AIF) indices, which are innovative markers of complex autonomic control extending the established HRV indices, will be explored based on previous developments and studies
[23,24,27,28].

### Key data acquisition and individual time line

Patients are enrolled on day 1 after admission (at most 24 hours after symptom onset). The following baseline data are documented: demographic data, medical history, medications prior to admission, vital signs (including blood pressure, NIHSS), stroke characteristics such as symptom onset as well as ischemia location and size obtained by cranial MRI or CT, blood parameters (CRP, WBC) at admission to the emergency unit.

For the HRV analysis a 24 h-Holter-ECG recording is started on the morning after the stationary admission around 9 h00 (at most 24 h hours after symptom onset). A second 24 h-Holter-ECG is applied on day 5.

Up to day 5 the neurological status (NIHSS, Rankin Scale, Barthel-Index), clinical signs of infection (fever, pathological findings of examination) and blood parameters (CRP, WBC, PCT, cortisol, ACTH, copeptine, IL-6, IL-10, mHLA-DR, TNFalpha) are documented in a daily visit.

After 3 months patients are interviewed via by telephone contact to record the clinical outcome (Modified Rankin Scale, Barthel-Index).

### Methods against bias

Patients eligible for the study will be recruited consecutively to prevent selection bias. HRV risk indices will be calculated according to standards and procedures previously developed and published by the applicant and blinded to the individual outcome diagnosis of the patients. Potential confounders like age, size of insult, localisation (laterality/insular cortex), use of beta blocker at admission, baseline NIHSS will be collected and included in the prognostic model according to a modelling procedure prespecified in a statistical analysis plan.

### Sample size

In a feasibility study 12 out of 34 patients (about 35%) with appropriate ischemic territorial stroke developed a new infection during day 3 to 5 after onset of stroke symptoms. Daytime LFnorm at baseline as a key HRV parameter was significantly lower in patients with infections compared to those without infections (mean = 40.1, SD = 19.4 and mean = 58.2, SD = 13.6, respectively). From the perspective of prognosis, an increase of LFnorm by one standard deviation (SD = 17.9) was associated with a 0.4 fold chance of getting an infection (OR = 0.4 or ln OR = β = -0.916). The logistic regression test of β =0 (α = 0.05 two-sided) will have 80% power to detect a β of -0.916 (OR = 0.4) with a sample size of 82 patients. To detect this effect while controlling for potential confounders sample size must be multiplied by the variance inflation factor 1/(1-σ^2^) where σ^2^ is the squared multiple correlation of LFnorm with further covariates in the model. A sample size of 136 will be necessary assuming σ^2^ = 0.4 and an infection proportion of 35% (nQuery Advisor 6.01).

According to the feasibility study 43% of patients had to be excluded after enrolment due to cardiogenic arrhythmias or ongoing infections at admission leaving about 57% of patients for the prognostic modelling. Therefore, a total of 240 patients should be allocated to the study.

### Feasibility of recruitment

Out of approximately 740 stroke patients admitted to the Department of Neurology per year about 170 meet the inclusion criteria, hence during 2 years of recruitment about 340 patients are available. Supposing that 70% to 80% of patients will consent to participate about 240 patients could be allocated to the study. These patients do not participate in competing studies.

### Statistical analysis

HRV risk indices (predictors) will be calculated from selected intervals of 24 h ECG measurements according to standards and procedures previously developed and published by the applicant. The predictive effects of HRV indices on infections will be estimated by fitting logistic regression models and estimating odds ratios with 95% confidence intervals. A prespecified modelling procedure will be applied to estimate unadjusted and confounder adjusted odds ratios. Secondary endpoints will be analysed in the same way. The functional outcome scales will be dichotomized. The association between HPV indices and pro- and anti-inflammatory molecular markers will be quantified by calculating the appropriate correlation coefficients according to scale (Person or Spearman).

### Ethical considerations

All stroke patients involved in this study are treated at the stroke unit according to the guidelines of the German Stroke Society (DSG) and German Neurological Society (DGN). Standard ECG measurements are non-invasive and without any risk for the patients. It is part of the standard medical assessment and is easily done at bedside. Laboratory investigations are without risk for the patient due to the minimal quantities required. The protocol was approved by the ethics commission of the University Hospital Jena. A written informed consent is obtained from all patients or their legal representatives. According to the ethics commission vote the written informed consent can be obtained retrospectively after the acute stroke period. In cases of decline the study data are deleted.

The study was registered at the German Clinical Trials Register (DRKS00003392).

### Recruitment

The recruitment, observation and follow-up of patients started in February 2012. All study related activities follow the study protocol and an elaborated study manual. It is planned to finish recruitment in May 2014.

## Discussion

The goal of this study is to show that HRV indices obtained in the acute post-stroke period are able to predict infections in the subsequent sub-acute period. HRV indices represent the role of ANS activity in connection with immunomodulation and developing infections after stroke. They would be readily available from routine ECG stroke monitoring systems. Their continuous consideration would allow an earlier identification and, hence, timely appropriate treatment of developing infections.

Recently, the clinical A^2^DS^2^ score to predict pneumonia in acute ischemic stroke was developed and validated using data of two independent stroke registers. This 10-point risk score (points) includes age ≥75 years (1), atrial fibrillation (1), dysphagia (2), male sex (1), stroke severity according to the National Institute of Health Stroke Scale 0–4 (0), 5–15 (3), ≥16 (5)
[29].

Biomarkers obtained from post-stroke blood samples, like WBC, CRP, PCT, and copeptin were all independent predictors of pneumonia, UTI, and other infections
[30]. Those authors concluded that “the combination of established inflammatory makers (WBC, CRP) combined with a biomarker of stress (copeptin) or a biomarker of bacterial infection (PCT) probably reflects better the complexity of an infection than one biomarker alone and may lead to a more accurate prediction of a beginning but not yet clinically apparent infection”.

In addition to the HRV indices all components of the A^2^DS^2^-score and the above mentioned blood markers are recorded in our study. We will be able to put our HRV study results into perspective by analysing several potential predictors and, depending on the number of observed outcome events, their combinations in multiple regression models.

## Abbreviations

ANS: Autonomous nervous system; CT: Computer tomography; HPA: Hypothalamo–pituitary–adrenal; MRI: Magnetic resonance imaging; NIHSS: National institutes of health stroke scale; OR: Odds ratio; SD: Standard deviation; SIRS: Systemic inflammatory response syndrome; UTI: Urinary tract infections.; AIF: Autonomic information flow; ECG: Electrocardiogram; HRV: Heart rate variability; HF: High frequency power; HFnorm: Normalized high frequency power; LF: Low frequency power; LFnorm: Normalized low frequency power; VLF: Very low frequency power.; ACTH: Adrenocorticotropic hormone; CRP: C-reactive peptide; IL-6: Interleukin 6; IL-10: Interleukin 10; HLA-DR: Monocytic Human Leukocyte Antigen-DR; PCT: Procalcitonin; TNFalpha: Tumor necrosis factor alpha; WBC: White blood cell count.
